#### Cognitive functioning

**General intelligence** is measured with a matrix reasoning task. This task involves 15 trials, where participants are presented with a 3 × 3 matrix with a missing piece and four options for the missing piece to pick from to best complete the matrix. The 15 matrix items, ranging from easy to quite difficult, were selected from the Matrix Reasoning Item Bank [34] to provide adequate differentiation. The total number of correct choices is summed, with participants’ performance compared to each other, as no norms for this selection of items exist.

**Working memory** facilitates learning, comprehension and problem-solving as it allows an individual to keep information in mind and use it to execute cognitive tasks. Working memory is assessed by a digit span task, where the participant is shown numbers one at a time in sequences of increasing length. The participant then tries to repeat the sequence by clicking numbers on the screen.

**Self-regulation** is the ability of an individual to flexibly apply situational rules and adjust his/her actions and expectations. To succeed, individuals must follow legal and cultural rules, regulate impulses, and apply different rules depending on contexts. Self-regulation is measured with one task per each of the three dimensions of self-regulation: a) Inhibition, b) Shifting, and c) Updating. *Inhibition* is measured with the Go/NoGo task [35] involving the ability to prevent a response or impulse. Most trials are “Go” or “Button Press” trials, however on the rare “No Go” trials, individuals must inhibit a button press. *Shifting* is measured with the Colour Shape Task [36], involving shifting between tasks flexibly. Trials randomly alternate between classifying by shape or by color. *Updating* is measured with the Corsi Task [37], which requires adding and deleting information in working memory. In this task, boxes light up in sequences, and individuals must then correctly click them in the same sequence. Each level adds difficulty by adding another box to the next new sequence.

**Decision making** is assessed with the Balloon Analog Risk Task [38]. In this task, participants collect points by inflating balloons. Each time the participant presses a button, a balloon inflates and the points value of the balloon in question is increased. However, the balloon also has a chance of exploding at each inflation. If the balloon explodes, the participant loses all points for that balloon. Instead of inflation, the participant can also choose to bank current points and move on to the next balloon. Different colored balloons with different chances of exploding are presented, and the participant may learn to assess the level of risks.

**Self-efficacy.** Self-efficacy is an individuals’ belief that through perseverance, they can reach a goal. Self-efficacy is also commonly referred to as ”grit” or ”motivation”. Self-efficacy is measured using the 10-item academic self-efficacy subscale of the Self-Efficacy Questionnaire for Children [39]. The subscale measures an individual’s conception of his/her own abilities related to success at school. Participants assess on a five-point scale how well each question describes their behavior (1 = *not at all* to 5 = *very well*).

#### Social functioning

**Social competence** is the ability to understand others’ emotional states and perspectives and use this information appropriately to guide decision making. Social competence is highly valued and rewarded in society both in personal relationships as well as peer group integration. Social competence is measured with two tasks, one each for emotion reading and theory of mind.

**Emotion reading** is measured with the Reading the Eyes task [40]. Photographs of eyes are presented together with four options for different emotions, and the participant must select the one matching the expression depicted. The share of correctly identified emotions yields a score of mentalizing accuracy.

**Theory of mind** is measured with The Yoni Test [41, 42]. In this test, children are presented with a series of trials where a cartoon outline of a face is looking at different objects or people around it. They must select the correct object or person the character is thinking about or has feelings towards based on its gaze, facial expressions or the facial expression of other faces it is referring to. Half the 64 trials require first-order and half second-order inference.

**Prosocial and altruistic sharing** is measured by the experimental protocol implemented in [43], extended from the work of Fehr et al. [44]. Each participant makes four choices between two options each. Each option describes an allocation of x units of rewards to the decision maker and y units to an anonymous recipient (of the same gender and roughly the same age). In each of the four choices, one allocation (x, y) is always the allocation (1, 1), while the alternative allocation was designed to classify different social preference types. The types are defined as follows: (1) altruistic if subjects maximize the recipient’s payoff in all four choices; (2) egalitarian if they always minimize the difference in payoffs for themselves and the recipient, which means to choose always the allocation (1, 1); (3) spiteful if they always minimize the recipient’s payoffs; and (4) selfish if they maximize their own payoffs in the first and the fourth choice (the payoff of the decision maker is the same in both options of the other two choices).

**Loneliness in the peer context.** The 16-item Peer Network and Dyadic Loneliness Scale (PNDLS) [45] is used to assess the students’ experiences of loneliness in peer relations on two levels, with 8 items each: peer network loneliness (i.e., loneliness associated with peer group isolation) and peer dyadic loneliness (i.e., loneliness associated with the absence of a close, enduring, emotionally intimate friendship with a specific other peer). The student reads two descriptions of different types of children and answers which describe them better. The student then evaluates on a two-point scale whether that description is *sort of true* or *really true* for them.

#### Mental health

**Resilience** is measured with the Individual Resiliences Questionnaire developed and found reliable in a previous study [33], after considering the well-validated Child and Youth Resilience Measure (CYRM) [46], but finding some of its items difficult for the target group of refugee children. The questionnaire consists of 10 items measuring the positive individual resources of children and adolescents. Participants evaluate on a three-point scale how well each description fits them (0 = *not at all*, 1 = *somewhat*, 2 = *yes, fits well*).

**Traumatization.** The Child and Adolescent Trauma Screen (CATS) [47] will be used to measure trauma exposure and trauma symptoms. This scale first measures exposure to 15 different potentially traumatic events. If the child has experienced any of these traumatic events, he/she will answer 20 items measuring posttraumatic stress symptoms. This screening test is based on DSM-5 criteria for PTSD and includes symptoms of re-experiencing, avoidance, negative alterations in mood and cognitions, and hyperarousal. The child answers on a 4-point scale how much the described symptoms have bothered them during the last two weeks (0 = *never*, 1 = *once in a while*, 2 = *half the time*, 3 = *almost always*).

**Depression** is measured with the Birleson Depression Self-Rating Scale (DSRS) [48]. This 18-item scale is based on an operational definition of depressive disorder, and the child answers on a 3-point scale how often (0 = *Mostly*, 1 = *Sometimes*, or 2 = *Never*) the statements have applied to them during the past week. The scale has been widely used across diverse ethnic and national groups [49].

All mental health measures have good reliability among war-affected children and adolescents [47, 50, 51] and we have used most of them in our previous studies among refugee children [10, 33, 52, 53].

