### Screening battery

The screening battery (SB) gathers many kinds of data about the participants using demographic survey questions, tasks, and questionnaires. The children answer questions and complete tasks, and data is also collected from parents and teachers. The battery contains standardized and universally applicable assessments of a) cognitive functions (general intelligence, working memory, self-regulation, and self-efficacy and decision making), b) mental health (symptoms and well-being), and c) social competence. Prior to T_1_, the research group will offer a half-day training to teachers and school psychologists participating in the study on how to use the screening battery and specifically its feedback function. During the training, initial ideas and resources on how to transform the feedback into supportive actions at schools will be discussed among participating teachers and school psychologists.

The screening battery uses the Gorilla online platform to administer questionnaires and tasks (https://gorilla.sc/). Results are then transferred via an API to a Microsoft Power BI feedback tool which compiles both anonymous general (for teachers) and personalized (for multiprofessional student welfare bodies with consent from children’s parents) feedback with data visualizations and recommendations for supportive measures for students. At the end of the school year, the SB is administered again for the same classes (T_2_). The data about any supportive actions (either using the information produced by SB or not) that children may have received during the school year is also collected. The data is collected from parents, teachers, and multiprofessional student welfare bodies. The child’s own experiences of the support received are also collected during follow-up measurements. The researchers, who are all licensed psychologists and specialists in child cognitive and social skills as well as in child mental health, will be available for consultations with the schools throughout the study year, in case the school has further questions or concerns.

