To test Hypothesis 3, screening battery effects on cognitive, social, and mental health functioning will be evaluated using repeated measures ANOVAs with 2 × 3 for {T_1_, T_2_} and {children who received SB-based support, children who received non-SB-based support, children who did not receive SB-based support} among children who scored above/under critical thresholds, and following up with *t*-tests to compare means. Differences in SB-based actions will also be evaluated qualitatively. We will further use linear regression to test whether changes in mental health (trauma- and depressive symptoms) and social functioning associate with changes in cognitive functioning from T_1_ to T_2_. In addition to analyses in the whole sample, we will also do these analyses by subgroup, separately for our three groups. Classroom atmosphere, teacher self-efficacy and awareness of culturally responsive education, family functioning, child language and development as well as children’s cultural background will be used as covariates in the regression analyses and ANOVAs. Effect sizes and confidence intervals will be reported for main effects and p-value based inference will be de-emphasized based on guidelines for New Statistics [60].

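### Trauma-symptom items are shown only after a reported event, and no carry-forward of T1 exposure to T2 is stated, so a changed exposure report can leave no usable T1–T2 symptom change

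*Protocol article*

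**What the plan says.** The Mental health section of the protocol article describes the trauma screen in two steps. "This scale first measures exposure to 15 different potentially traumatic events". Then: "If the child has experienced any of these traumatic events, he/she will answer 20 items measuring posttraumatic stress symptoms". The symptom items have a short recall window: "The child answers on a 4-point scale how much the described symptoms have bothered them during the last two weeks", each scored 0 to 3.

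The Screening battery section repeats the instrument: "At the end of the school year, the SB is administered again for the same classes". It describes no different T2 version of the trauma scale. Elsewhere the article does mark what is particular to T2: life changes and the child's list of support received (Tests and measures), life changes and use of the battery's output (Parental report), and use of that output and classroom actions (Teacher report).

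The Analysis plan uses the T1–T2 change twice. For Hypothesis 3, "screening battery effects on cognitive, social, and mental health functioning will be evaluated using repeated measures ANOVAs with 2 × 3" (time by support group), and this is done "among children who scored above/under critical thresholds". A linear regression then asks "whether changes in mental health (trauma- and depressive symptoms) and social functioning associate with changes in cognitive functioning".

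**The concern.** A change score needs the same questions answered at both times. Here, whether a child sees the symptom questions depends on another answer, the event list, and that answer may differ between autumn and spring. A child's history does not shrink over a school year, but what the child reports can change.

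If the T1 routing is reused unchanged at T2, two kinds of discordant reporter arise:

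- **Event at T1, none at T2.** The symptom items are skipped at T2, so there is no T2 score.
- **No event at T1, event at T2.** The symptom items were skipped at T1, so there is no baseline.

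The first kind matters more for Hypothesis 3. A child who enters that analysis because of a high T1 trauma-symptom score must have passed the T1 gate. For such a child, a changed exposure report can only remove the T2 score or, under zero scoring, set it to 0. The loss may also be related to support. Assessment is in the classroom, and individual results may go to the student welfare body and be discussed with the child, so a child whose T1 answers were acted on may answer the event list differently later.

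This is a data-collection matter. A later analysis plan can choose how to score skipped items, but it cannot recover answers that were never requested.

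**Working it through.** **1. The plan's own figure.** The only computable figure is the sample size: about 150 per group for d = 0.5, ICC 0.07, alpha 0.05 and 80% power, with cluster size 17 and variance 10. Taking alpha as two-sided:

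- Without clustering, 63 per group are needed.
- The design effect with unequal clusters is 1 + ((1 + 10/17²) × 17 − 1) × 0.07 = 2.161.
- 63 × 2.161 = 136.2, so 137 per group by the normal approximation.
- A noncentral t calculation with cluster-level degrees of freedom gives power 0.797 at 9 clusters of 17 (153 per group), which agrees with the stated figure.

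This point does not affect the sample size. The figure d = 0.5 serves below only as a yardstick.

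**2. Inputs for the size of the problem.** The article gives none of the following, so all are assumptions:

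- q: share of T1 disclosers who deny every event at T2. Range 5% to 20%.
- M: mean symptom score among T1 disclosers. Base value 15, range 15 to 25, on a 0–60 sum (20 items × 3; sum scoring is itself assumed).
- SD of that score: base value 10, range 10 to 12.
- True symptoms do not change, and children lost at T2 have the average score.

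**3. If skipped items are left missing.** Of every 100 T1 disclosers, 5, 10 or 20 change pairs are lost at q = 5%, 10% or 20%. Any bias depends on whether these children's true change differs from the others', which cannot be computed from the article.

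**4. If skipped items are scored 0: change within one group.** False improvement = q × M / SD.

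| q | M = 15, SD = 10 | Low: M = 15, SD = 12 | High: M = 25, SD = 10 |
|---|---|---|---|
| 5% | 0.075 | 0.0625 | 0.125 |
| 10% | 0.15 | 0.125 | 0.25 |
| 20% | 0.30 | 0.25 | 0.50 |

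**5. If skipped items are scored 0: the Hypothesis 3 contrast.** Hypothesis 3 compares change between support groups, so a loss rate common to all groups cancels. False difference = (q_A − q_B) × M / SD.

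- 10% versus 5%: 0.05 × 15/10 = 0.075 SD (range 0.0625 to 0.125), or 15% of d = 0.5.
- 20% versus 5%: 0.15 × 15/10 = 0.225 SD (range 0.1875 to 0.375), or 45% of d = 0.5.
- Equal rates: 0.

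**6. Reverse case.** A child who first discloses at T2 has no change score if the T1 items are left missing. The child looks like a deterioration only if they are scored 0. The share of such children is also unknown.

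**The case against.** The strongest objection is that the article never describes T2 routing. A reader might infer that at T2 the symptom items appear only for children who report an event on that day, but no sentence says so. The gate is worded as having experienced an event, which is a lasting status. A child recorded as exposed at T1 still meets it at T2, so carrying the answer forward would fit the text. This stands, and the point is therefore conditional. Even so, re-applying the gate is the plain reading: the scale asks exposure first, the battery is given again, and the article names other T2 differences but none for this scale.

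A reader might also infer that such a child appears recovered. That needs a zero-scoring rule, and the article gives none. With missing scoring the pair is incomplete and nothing more.

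A condensed article may leave scoring and discordant reports to fuller documents, and a preregistration and a pilot are announced. That is fair for scoring. It is weaker for routing, because the article itself describes who is asked the symptom items and that choice fixes which data exist.

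On size, three objections stand. Every input is assumed. A child must deny all 15 events to be lost, so children with several exposures are the least likely to be affected. If those lost have milder symptoms, the zero-scoring effect is smaller. The direction is also uncertain, because trust and support could raise T2 disclosure instead of lowering it.

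Finally, T1 trauma scores and the ungated depression and resilience scales could support imputation or sensitivity analyses. They reduce the loss under assumptions but do not replace the missing answers.

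**Conclusion.** The concern holds in conditional form. The article gates the symptom items on exposure, repeats the battery, analyses change in trauma symptoms, and states no carry-forward of T1 exposure. If the gate is re-applied as it stands, trauma change is undefined for children whose exposure report differs between T1 and T2, and it is false where skipped items are scored 0.

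The size could be trivial or material, because the rate of discordant reporting is unknown. A reader might set the 0.30 SD within-group figure against the planned d = 0.5 as the bias in Hypothesis 3. The design does not support that comparison: it would need 20% loss in one support group and none in another. With M = 15, SD = 10 and zero scoring, the contrast moves by 0.075 SD for 10% versus 5% and by 0.225 SD for 20% versus 5%. The change is worth making because it is cheap and must be settled before T2 data are collected. The sample size and the baseline comparisons are unaffected.

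**What to change.** State the T2 routing and the scoring of skipped items:

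1. At T2, route to the 20 symptom items every child who endorsed at least one event at T1 or at T2, carrying the T1 answer forward in the online platform.
2. Treat skipped symptom items as not asked, never as 0.
3. Base trauma-change analyses on children who were asked the symptom items at both times.
4. Report children who first disclose at T2 separately.
5. Flag T2 symptom answers from children who deny all events at T2, and show the results with and without them.

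The cost is one branching rule and a few extra minutes for a small number of children. The downside is that a few children who have just denied every event are still asked about symptoms, and their answers are harder to interpret. Step 5 is there for that reason.

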#### Parental report

**Demographic variables.** At T_1_, we ask background information such as parents’ age, country of birth, education, marital status, and housing arrangements are collected. We also ask parents to report on the child’s country of birth, current legal status in host country, time in host country, and reason of migration. We request this information from both parents and children. Parents would be more reliable informants on these questions, but in the likely situation that we are unable to reach all parents, we will have the child’s report on the same topics. If there is discrepancy in child and parent reports, we rely on parents’ report. At T_2_, we ask about significant life changes after T_1_. The questionnaire includes changes in legal status in host country, family composition, significant losses, or other changes in close relations and other significant life changes. At T_2_, we collect information on whether or not the information provided by the SB has been used for the child, and a list of supportive actions the child or family has received.

**Family functioning** is measured by 12 items from the General Functioning subscale of the McMaster Family Assessment Device (FAD) [54, 55]. The parent assesses on a four-point scale how much they agree with the descriptions of family functioning (0 = s*trongly agree*, 1 = a*gree*, 2 = d*isagree*, 3 = s*trongly disagree*).

**Child language and development** is measured by 10 selected items from the Alberta Language and Development Questionnaire (ALDeQ) [56]. The selected items were chosen to reflect the parents’ view of the general development of the child and possible challenges in it, as well as parents’ own reading or learning difficulties. The parent evaluates each item on a four-point scale, but due to the varying form of the items, the answer categories vary between items (such as 0 = *never*, 1 = *rarely*, 2 = *sometimes*, 3 = *very much* or 3 = *very easy*, 2 = *easy enough*, 1 = *sometimes not easy*, 0 = *no, very hard*).

#### Teacher report

**Teacher self-efficacy** in the classroom is measured by Teachers’ Sense of Efficacy Scale (TSES). The TSES is a 12-item questionnaire, where teachers indicate on a 9-point scale how much they can do as teachers in each of the situations described (1 = *nothing*, 3 = v*ery little*, 5 = s*ome influence*, 7 = *quite a bit*, 9 = *a great deal*).

**Teachers' view of children’s co-operation skills and classroom atmosphere.** This quality is measured with a 9-item questionnaire developed in the Yhteispeli project in Finland [57]. Teachers respond on a 5-point scale how well the statements fit him/her.

At T_2_, we collect information on whether or not the information provided by the SB has been used and a list of supportive actions in the classroom.

**Teachers’ beliefs and perspectives on teaching for social justice** are measured with nine items of the original 12-item Learning to Teach for Social Justice-Beliefs (LTSJ-B) scale [58], because the nine-item adaptation has previously been adapted and found suitable for the Finnish school context [59]. The teachers assess items related to culturally responsive education on a five-point scale (1 = s*trongly agree*, 2 = a*gree*, 3 = *I don’t know*, 4 = d*isagree*, 5 = s*trongly disagree*).

#### Analysis plan

**Power.** In order to form profiles across different groups of children and to assess changes in cognitive, social, and mental health functions across those children who will receive SB based supportive actions and those who do not, we performed a preliminary power analysis to determine the sample size required to detect medium-sized or larger effects on these primary outcomes. Based on typical sizes of Finnish preparatory classes, we estimated the average size of each cluster to be 17, with a variance of 10. Intraclass coefficients for these outcomes are challenging to estimate, but based on our previous cluster-randomized research among war-affected children, values of 0.01–0.1 could be reasonable. With a relatively conservative estimate of 0.07 for the ICC, and setting alpha at 0.05, to achieve 80% power to detect a medium-sized (d = 0.5) or larger effect, we would need about 150 children in each group, meaning approximately 450 children in total.

**Analyses.** Means, standard deviations, and correlations will be evaluated for all variables reported by children, parents, and teachers. To test Hypothesis 1, baseline differences between the study’s three groups will be investigated using 3-way ANOVAs and followed up with *t*-tests to compare means. To test Hypothesis 2, correlation analyses will first be used to examine whether mental health (trauma-related and depressive symptoms) is associated with poorer cognitive function and social competence. Latent profile analyses (using the TidyLPA package in R) will then be run for the entire sample under each of the three dimensions: cognitive, social, and mental health. Emerging profiles will be compared with how they line up with our three groups (refugee, immigrant, native-born Finnish).

To test Hypothesis 3, screening battery effects on cognitive, social, and mental health functioning will be evaluated using repeated measures ANOVAs with 2 × 3 for {T_1_, T_2_} and {children who received SB-based support, children who received non-SB-based support, children who did not receive SB-based support} among children who scored above/under critical thresholds, and following up with *t*-tests to compare means. Differences in SB-based actions will also be evaluated qualitatively. We will further use linear regression to test whether changes in mental health (trauma- and depressive symptoms) and social functioning associate with changes in cognitive functioning from T_1_ to T_2_. In addition to analyses in the whole sample, we will also do these analyses by subgroup, separately for our three groups. Classroom atmosphere, teacher self-efficacy and awareness of culturally responsive education, family functioning, child language and development as well as children’s cultural background will be used as covariates in the regression analyses and ANOVAs. Effect sizes and confidence intervals will be reported for main effects and p-value based inference will be de-emphasized based on guidelines for New Statistics [60].

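### The 80% power for d = 0.5 is sized for the three background groups and does not carry over to Hypothesis 3, although the power paragraph says it covers the support comparison

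*Protocol article*

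**What the plan says.** The Power paragraph of the Analysis plan names two purposes: forming profiles across groups of children, and assessing change in cognitive, social and mental health functions "across those children who will receive SB based supportive actions and those who do not". Its inputs follow. On class size, "we estimated the average size of each cluster to be 17, with a variance of 10". On the ICC, "values of 0.01–0.1 could be reasonable", and then "With a relatively conservative estimate of 0.07 for the ICC", "setting alpha at 0.05". The target is "to achieve 80% power to detect a medium-sized (d = 0.5) or larger effect", and the result is "we would need about 150 children in each group, meaning approximately 450 children in total".

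The section Participants and procedure allocates the three sets of 150 to refugee, non-refugee immigrant and native-born Finnish children. A second recruitment year is triggered only if one of these background groups falls short.

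The Analyses paragraph tests Hypothesis 3 by a repeated measures ANOVA, two time points by three support categories (SB-based support, other support, no SB-based support), "among children who scored above/under critical thresholds", with follow-up t-tests. It then repeats the analyses separately in each background group. The article gives no expected share beyond threshold, no expected size of the support categories and no T1–T2 correlation.

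**The concern.** The word group means two different things. In the sample size result it is a background group, whose size the study controls through recruitment. In Hypothesis 3 it is a support category, whose size depends on how many children cross a threshold and on what the schools then do. Nothing in the design controls or estimates the second kind, yet the power paragraph names that comparison as one it was sized for.

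Hypothesis 3 is the only hypothesis about whether acting on the screening battery helps, and the Discussion promises evidence on it. If its result is imprecise, a reader will set it against a stated 80% power for a medium effect that was never calculated for that comparison. The same holds, more strongly, for the question in the Research question section of whether the effect differs between background groups.

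**Working it through.** **Inputs from the plan.** d = 0.5; alpha 0.05 (two-sided assumed, as the side is not stated); power 80%; ICC 0.07, range 0.01 to 0.1; class size m = 17 with variance 10, so CV² = 10/17² = 0.035.

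**1. Reproducing 150.**
- Unclustered: n = 2(1.96 + 0.84)²/0.5² ≈ 63 per compared group.
- Design effect: 1 + [17 × 1.035 − 1] × 0.07 = 2.16 (2.12 with equal classes).
- Normal approximation: 63 × 2.12 to 63 × 2.16 = 134 to 136 per group.
- Noncentral t with class-level degrees of freedom, 2(k − 1) for k classes per group: about 152 to 154 per group. Nine whole classes (153 children) give power 0.80.

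The stated 150 is therefore right as a two-group comparison with 150 in each compared group. Over the plan's ICC range, 150 against 150 gives the following. The lower figure uses class-level and the upper child-level degrees of freedom.

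| ICC | Power at d = 0.5 |
|---|---|
| 0.01 | 96–98% |
| 0.07 | 79–84% |
| 0.10 | 70–75% |

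**2. What Hypothesis 3 would need.** With three support categories, 150 per category means 450 analysed children: all flagged, evenly split and all seen at T2. If fewer are flagged, fewer children per class are analysed and the design effect falls. Allowing for that, 80% power still needs about 80% of all children flagged (120 per category; design effect about 1.9; power 0.80).

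**3. Within one background group.** An equal three-way split of 150 gives at most 50 per category, even with every child flagged. For d = 0.5 on the scale tested, power is 39% with ICC 0.07 and m = 17 (design effect 2.16), and 70% with no clustering. No flagging rate reaches 80% on this scale with an equal split.

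**4. Whole sample, as an illustration.** Assumptions that the documents do not give: share flagged f = 20–48%, equal split, d on the scale tested. The Background section reports 20–48% for PTSD and depression in refugee children; it is borrowed here only to set a range. Children per category = 450f/3, or 150f/3 within one background group. Design effect = 1 + [17f × 1.035 − 1] × 0.07, which is 1.18 at f = 20% and 1.52 at f = 48%. This treats flagged classmates as sharing a support type.

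| | n per category | Power, ICC 0.07 | Power, no clustering |
|---|---|---|---|
| Whole sample | 30–72 | 42–68% | 48–85% |
| One background group | 10–24 | 16–28% | 18–40% |

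The effect detectable with 80% power under clustering, (1.96 + 0.84)√(2 × design effect/n), is 0.78 to 0.58 in the whole sample.

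**5. Sensitivity.**
- T1–T2 correlation: if d = 0.5 is in raw SD units and change is analysed, the effect on the change scale is 0.5/√(2(1 − r)). At r = 0.5 this is 0.5 and nothing changes. At r = 0.7 it is 0.65, and power with clustering is 62–88% overall and 24–43% within a background group. At r = 0.8 overall power is 79–97%.
- Support mixed within classes: if each class's flagged children divide evenly over the three categories, whole-sample power is 47–80%.
- Uneven split: at f = 20%, one category with 20% of the flagged children against another with 40% gives 35% in place of 42%.

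**The case against.** The strongest reply is that the low percentages come from inputs the plan does not contain. The thresholds span cognitive, social and mental health measures, so the flagged share could be well above or below a range quoted for PTSD and depression in refugee children. The test is a repeated measures one, and crediting a strong T1–T2 correlation can bring whole-sample power above 80%. Individual reports go to welfare bodies child by child, so support may differ within a class and clustering may cost little. All of this stands. It rules out a stronger reading that a reader might infer, namely that Hypothesis 3 is known to have 42–68% power, or that whole-sample power must be below 80%. The documents support neither.

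Nor is there a calculation error: the 150 reproduces. The paragraph calls its analysis preliminary, and 0.07 lies in the upper half of the plan's ICC range, so describing it as relatively conservative is fair wording. Allowance for loss by T2 may sit in a fuller document. Neither point carries weight here.

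The plan also says that p-value inference will be de-emphasised in favour of effect sizes and confidence intervals. That softens the risk that a null result is misread, but low power then shows as wide intervals, and the stated 80% still describes another comparison.

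What the reply does not remove is the mismatch itself. The article explicitly attaches its power calculation to the support comparison, while its own recruitment and analysis sections size and define something else.

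**Conclusion.** The point holds as a fault of scope. The 80% power for d = 0.5 applies to comparisons between background groups of 150 and not to Hypothesis 3, whose categories come from a threshold-selected subset of unstated size.

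The firmest figure is the one within a background group: at most 50 per support category under an equal split, so about 39% power with the plan's ICC and class size, or 70% with no clustering. It rests on d being on the scale tested. With r = 0.7 and every child flagged, the same calculation gives just under 60% with clustering and about 89% without, so the ceiling is not absolute, but it would need both favourable conditions at once.

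The whole-sample figures illustrate how far power could fall and are not estimates of it. The baseline comparisons of Hypothesis 1 are not called into question at the plan's ICC of 0.07.

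**What to change.** Restate the power paragraph in three steps.

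1. Limit the 80% / d = 0.5 statement to the background-group comparisons, and show it over the plan's own ICC range (about 96–98% at 0.01, 79–84% at 0.07, 70–75% at 0.10).
2. For Hypothesis 3, give power or the detectable effect as a range over stated assumptions: share flagged, split over the support categories, clustering, and T1–T2 correlation, with the scale of d named. The spring 2024 pilot may inform the share flagged.
3. Label the Hypothesis 3 analyses within each background group as exploratory.

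This changes wording only. Enrolment, measurements and analyses stay as planned. The cost is a less favourable stated figure for Hypothesis 3.
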